### 2.5. Assessment/Outcome Variables

The primary outcome of the INTERAPNEA study is the reduction in the number of apnoea and/or hypopnoea episodes per hour, i.e., AHI, assessed using a full-night ambulatory polysomnography. The main secondary outcomes include other neurophysical and cardiorespiratory polysomnographic outcomes, body weight and composition, physical fitness/cardiorespiratory fitness, and health blood biomarkers. Other variables of interest are subjective measurements of depressive and anxiety symptomatology related to OSA, impaired sleep (i.e., daytime sleepiness, sleep quality, and functional outcomes of OSA), health-related quality of life, and other lifestyle habit measurements (i.e., diet, physical activity, alcohol and tobacco consumption). All outcomes will be measured at baseline (week 0), intervention end-point (week 9), and 6 months post-intervention (week 32).

Assessment of primary and secondary outcomes will be organised and completed over three different days during a one to two-week period:Day 1: Potential participants will attend a medical examination and a fasting blood test at the Sleep Unit of “Virgen de las Nieves” University Hospital.Day 2: Eligible participants will complete a full-night in-laboratory polysomnography (PSG; the gold-standard objective testing recommended by the AASM [29]), at the Sleep and Health Promotion Laboratory (CIMCYC). In order to avoid potential CPAP influence on PSG outcomes, participants will be required to withdraw from CPAP during the week prior to the PSG at baseline and follow-ups [30]. Prior to PSG, participants will also complete a set of questionnaires measuring subjective variables related to sleep, general physical and psychological health, and lifestyle habits including diet, physical exercise, and alcohol and tobacco consumption.Day 3: During the third and last assessment day, participants will be required to attend the iMUDS for the measurement of anthropometric parameters, body composition and cardiorespiratory fitness.

Baseline physical activity and sleep habits will also be obtained through a seven-day self-reported daily step log and sleep diary. See Table 2 for study outcomes and measurements.

#### 2.5.1. Primary Outcome: Apnoea-Hypopnoea Index

The primary outcome of the INTERAPNEA study is AHI, defined as the number of apnoea (90% or greater drop in airflow for 10 s or longer) and hypopnoeas (30% or greater drop in airflow for 10 s or longer associated with ≥3% oxygen desaturation or an arousal) episodes per hour of sleep [31].

We will measure this outcome and other neurophysical and cardiorespiratory secondary outcomes through an in-laboratory PSG using SOMNOScreen™ PSG-Tele (SOMNOmedics, GmbH, Randersacker, Germany), or Somté PSG v2 system (Compumedics Limited, Abbotsford, Australia). The recordings will include all recommended physiologic signals such as electroencephalogram (three channels: F4-M1, C4-M1, O2-M1), electrooculogram (two channels: E1 and E2), electromyogram (two channels: submental and anterior tibialis muscles), and electrocardiogram (two channels). Cardiorespiratory measurements will include oral and nasal airflow (triple thermistor), oxyhaemoglobin saturation (SpO_2_) and pulse-rate (pulse oximeter), respiratory effort (chest and abdomen bands), and body position (sensor). All electrodes will be placed in accordance with the international 10–20 system [32], and recordings will be automatically and manually scored in 30 s epochs [33] by trained physicians using DOMINO (v2.7, SOMNOmedics, GmbH, Randersacker, Germany), or ProFusion PSG 3 (v3.3, Compumedics Limited, Abbotsford, Australia) associated computer software. All parameters, settings, filters, technical specifications, sleep stage scoring and event scoring will be performed in accordance with the AASM Manual for the Scoring of Sleep and Associated Events [31].

We will also specifically analyse AHI in rapid eye movement (REM) and non-REM sleep stages (N1, N2, and N3). Although it has been shown that REM apnoea episodes may yield more adverse cardiovascular consequences than non-REM obstructions [34], previous similar RCTs have rarely included the reduction in AHI differentiated by these sleep stages [1].

#### 2.5.2. Secondary Outcomes

##### Neurophysical and Cardiorespiratory Polysomnographic Outcomes

Secondary polysomnographic outcomes related to OSA measured by PSG, as mentioned above, are oxygen desaturation index (number of oxygen desaturation ≥3% per hour), SpO2 mean (average of oxygen saturation), SpO2 nadir (minimum oxygen saturation), arousal index (number of arousal per hour), total sleep time, sleep efficiency (total sleep time/total time in bed), sleep latency, wake after sleep onset (number of awakenings), REM sleep stage, REM latency, nonREM sleep stages (N1, N2, and N3), periodic limb movements index (PLMI; periodic limb movements per hour of sleep), and heart rate variability (HRV)/ST segment changes.

##### Physical Fitness

Cardiorespiratory fitness will be measured through a 2 km walking test, which has been widely used and validated for accurate estimation of maximum oxygen uptake (VO_2max_) [35]. Participants will be required to walk over a marked 2 km track on a firm surface wearing a heart rate monitor (Polar RS800cx, Polar Electro, Kempele, Finland). Walking time and heart rate (HR) will be recorded at the end of the test. The maximal aerobic power will then be calculated considering age, BMI, performance time, and HR with the following formula $VO_{2max}\left(\left(ml/min\right)/kg\right)=116.2-2.98*walking\;time\;\left(\sec\right)-0.11*HR-0.14*age-0.39*BMI$ [36]. Participant’s scores will be obtained and placed within a fitness category. Subjective physical fitness will also be measured using the International Fitness Scale (IFIS) [37].

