### 2.3. Participants and Selection Criteria

Eligible participants will be adults previously diagnosed with moderate to severe OSA (AHI equal or greater than 15 [22]) from the province of Granada (Spain). They must be between 18 and 65 years old, and have a body mass index (BMI) equal to or greater than 25 kg/m^2^. A full list of the study’s inclusion and exclusion criteria are shown in Table 1. Due to the well-evidenced higher incidence and prevalence of OSA in males [9], and the differences in OSA phenotypes between men and women [23], we decided to include only male participants in the study. Furthermore, the effectiveness of non-pharmacological and non-surgical weight loss interventions have been shown to be less effective in women [1,24], such that different approaches are needed in this population with OSA.

Potential participants will be medically examined and must complete a health history revision prior to their inclusion in the study in order to ensure no hindrance/harm related to the assessment and intervention protocols. Should any incident or medical problem arise during the intervention, participants will be physically and psychologically examined and, if necessary, excluded from the study. A clinical trial liability insurance will be contracted for the INTERAPNEA study, providing legal and financial protection to the sponsor-investigators, and compensation to participants in the case of an injury or any damage incurred in and as a result of the study.

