## Figures and Tables

**Figure 1 nutrients-11-02227-f001:**
[figure not shown]
Flow diagram of the INTERAPNEA study participants.

**Table 1 nutrients-11-02227-t001:** Eligibility criteria.

Inclusion Criteria	Exclusion Criteria
Men aged 18–65 years CPAP-treated moderate to severe OSA (AHI equal to or greater than 15 events/h) BMI equal to or greater than 25 kg/m^2^ Not participating in a weight loss program Willing to provide informed consent and acceptance of random group assignment	Presence of any other primary sleep disorder Presence of any mental disorder (including depression, anxiety, and addiction to alcohol or other substances) Presence of any other severe organic disease, except for those comorbid to OSA Regular use of neuroleptic, sedative or hypnotic drugs, or any other medication that may cause sleep disturbances or increased daytime sleepiness

AHI = apnoea-hypopnoea index; BMI = body mass index; CPAP = continuous positive airway pressure; OSA = obstructive sleep apnoea.

**Table 2 nutrients-11-02227-t002:** INTERAPNEA study outcomes and measurements.

Variable	Measurement	Assessment
General health history and sociodemographic information	General medical examination (i.e., anamnesis, physical exploration, vital measurements, etc.)	Week 0
	Clinical and socio-demographic interview	Week 0
	Fasting blood test	Week 0, 9, 32
Sleep quality and health-related quality of life		
Sleep habits	Sleep diary	Week 0, 9, 32
Circadian preference/chronotype	Morningness-Eveningness Questionnaire	Week 0, 9, 32
Sleep quality	The Pittsburgh Sleep Quality Index	Week 0, 9, 32
Daytime sleepiness	Epworth Sleepiness Scale	Week 0, 9, 32
	Psychomotor Vigilance Test	Week 0, 9, 32
Perceived health-related quality of life	Sleep Apnea Quality of Life	Week 0, 9, 32
	Short-Form 36 Health Survey	Week 0, 9, 32
	General Health Questionnaire	Week 0, 9, 32
Objective sleep		
Neurophysiological outcomes	Polysomnography equipment	Week 0, 9, 32
Cardiorespiratory outcomes	Polysomnography equipment	Week 0, 9, 32
Body weight and composition		
BMI and anthropometric measurements	Weight and height measurement, and neck, chest and waist circumferences	Week 0, 9, 32
Body composition	Dual Energy X-ray Absorptiometry	Week 0, 9, 32
Lifestyle habits		
Physical exercise habits	Spring-levered pedometer and daily step logs	Week 0, 9, 32
Dietary habits	Food Behaviour Checklist	Week 0, 9, 32
	Mediterranean Diet Adherence Screener	Week 0, 9, 32

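### The VO2max equation takes walking time in seconds, so every participant would get an impossible negative value for a main secondary outcome

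*Protocol article*

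**What the plan says.** Section 2.5 of the protocol article ranks cardiorespiratory fitness among the main secondary outcomes: "The main secondary outcomes include other neurophysical and cardiorespiratory polysomnographic outcomes, body weight and composition, physical fitness/cardiorespiratory fitness". Table 2 schedules the 2 km walk test at weeks 0, 9 and 32.

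The Physical Fitness part of section 2.5.2 describes the test ("Participants will be required to walk over a marked 2 km track on a firm surface"), says that walking time and heart rate are recorded at its end, and then gives the derivation: "The maximal aerobic power will then be calculated considering age, BMI, performance time, and HR with the following formula". The right-hand side of the formula is "116.2-2.98*walking\;time\;\left(\sec\right)-0.11*HR-0.14*age-0.39*BMI", and the left-hand side is VO2max in ml per minute per kg. The result is then used a second time: "Participant’s scores will be obtained and placed within a fitness category".

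The article does not repeat the equation elsewhere, state walking time in minutes, or convert seconds to minutes.

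**The concern.** The intercept is 116.2, and walking time is multiplied by 2.98. If time is counted in seconds, any realistic time for 2 km makes the subtracted term many times larger than the intercept, and the estimated oxygen uptake is negative. That is physically impossible and cannot be placed in any fitness category.

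The error is more than a change of scale. Using seconds multiplies the time term by 60 and leaves the heart rate, age and BMI terms as they are. The score then becomes almost a pure function of walking time, and the other three terms nearly vanish. A between-arm difference in this variable would describe a different quantity from the intended one. On the raw scale, the part due to walking time would be 60 times too large.

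**Working it through.** **Inputs from the protocol article.** The coefficients, the unit of time and the 2 km distance come from the Physical Fitness part of section 2.5.2. For age, section 2.3 says "They must be between 18 and 65 years old"; for BMI, Table 1 says "BMI equal to or greater than 25 kg/m^2". The article states no VO2max value, so there is no published figure to reproduce.

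**Inputs assumed.** A 2 km walking time of 15 to 20 min (900 to 1,200 s), an end-of-test heart rate of 110 to 160 bpm, and an upper BMI of 40. The article gives none of these.

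**Step 1: a bound that needs no assumption about participants.** Heart rate, age and BMI are all subtracted, so setting them to zero gives the largest possible result. It is positive only if

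116.2 - 2.98 × T > 0, that is T < 116.2/2.98 = 39.0 s.

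Covering 2,000 m in 39.0 s means 51.3 m/s, or about 185 km/h. Every participant therefore gets a negative value.

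**Step 2: size for one illustrative participant** (age 50, BMI 33, heart rate 130). The part of the formula without time is

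116.2 - 0.11 × 130 - 0.14 × 50 - 0.39 × 33 = 116.2 - 14.30 - 7.00 - 12.87 = 82.03.

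| Walking time | Time term, seconds | VO2max as printed | Time term, minutes | VO2max with minutes |
|---|---|---|---|---|
| 15 min (900 s) | 2,682.0 | -2,600 | 44.70 | 37.3 |
| 18 min (1,080 s) | 3,218.4 | -3,136 | 53.64 | 28.4 |
| 20 min (1,200 s) | 3,576.0 | -3,494 | 59.60 | 22.4 |

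**Step 3: range over the assumed values.**

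- Highest value (15 min, heart rate 110, age 18, BMI 25): -2,590.2 as printed; with minutes, 116.2 - 44.7 - 12.1 - 2.52 - 9.75 = 47.1.
- Lowest value (20 min, heart rate 160, age 65, BMI 40): -3,502.1 as printed; with minutes, 116.2 - 59.6 - 17.6 - 9.1 - 15.6 = 14.3.

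With minutes, the range of about 14 to 47 ml/min/kg is physiologically plausible. This points to a wrong unit label and not to wrong coefficients.

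**Step 4: effect on differences.** One minute off the walking time changes the printed score by 2.98 × 60 = 178.8, against 2.98 with time in minutes. As printed, 1 kg/m² of BMI (0.39) counts the same as 0.39/2.98 = 0.13 s of walking. With minutes it counts the same as 0.13 min, about 8 s.

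**The case against.** The strongest reply accepts that the label is wrong and disputes how much it matters.

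- **Reach.** The slip touches one derived secondary variable. The primary outcome is AHI, and neither the sample size in section 2.4.1 nor the analysis of AHI uses VO2max. This stands.
- **Recoverability.** Walking time and heart rate are recorded, so VO2max can be recalculated without new data, and a column of large negative values would be noticed. This also stands.
- **Text or calculation.** The equation cites a source, and the trial's own code may already use minutes. That is possible, but the article does not say so, and it gives no other statement of the derivation. Condensing a full protocol explains an omission; it does not explain a formula that is stated wrongly.
- **Overstatement.** The printed score would still rank participants roughly by speed. The 60-fold inflation applies only to raw units: the Cohen's d planned in section 2.9 divides by the baseline standard deviation, and a test statistic does not depend on scale. This is correct. For standardised results the damage is the altered weighting shown in Step 4.
- **Walking time.** A value near -3,000 rests on an assumed walking time of about 17 min. The impossible sign does not, as Step 1 shows.

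**Conclusion.** The equation is wrong as printed. That every participant would receive a negative VO2max follows from the article's own coefficients and distance alone. The size, about -2,600 to -3,500 ml/min/kg, assumes a walk of 15 to 20 min. The inference that minutes were intended rests on the plausible values obtained with the same coefficients, and it should be confirmed against the cited source.

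The consequence is confined to one main secondary outcome and the fitness categories built on it. The trial's main conclusion is not at risk, and nothing shows that the trial's actual calculations use seconds. The correction should still be made before the variable is derived, because the outcome cannot be used as defined.

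**What to change.** Replace the seconds label in the Physical Fitness equation with decimal minutes, or write explicitly that seconds are divided by 60. Before doing so, check the coefficients and the unit against the source that the article cites for the equation, and confirm that the analysis code uses the same unit. Add a range check to the derivation so that negative or otherwise implausible values are flagged.

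An optional addition, separate from the unit error, is to report 2 km walking time and end-of-test heart rate beside VO2max. BMI is a term in the equation, so each 1 kg/m² lost raises the estimate by 0.39 ml/min/kg with no change in walking time or heart rate. In a weight-loss trial, the two components help to separate a fitness gain from weight loss.

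The cost is a correction to one unit label and a short check. The optional part adds two variables that are already collected to a table. No new data are needed, and the design does not change.

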##### Body Weight and Composition

Body weight and height will be measured using a calibrated scale and stadiometer (model 799, Electronic Column Scale, Hamburg, Germany) with participants wearing undergarments. Neck, chest and waist circumferences will also be measured following standard procedures recommended by the International Society for the Advancement of Kinanthropometry (ISAK) [38]. Body composition measurements including fat mass (kg), fat free mass, lean mass (kg), visceral adipose tissue (kg), and bone mineral density (g/cm^2^) will be obtained through a full-body dual energy X-ray absorptiometry (DXA) scanner (Discovery Wi, Hologic, Inc., Bedford, MA, USA). Quality controls, positioning of participants and analyses of results will be performed following the manufacturer’s recommendations. Automatic delineation of anatomic regions will be performed using APEX 4.0.2. software.

##### Blood Biomarkers

Blood samples will be obtained from participants’ antecubital vein in a supine position during the morning in a fasting state. Blood parameters will include insulin, glucose, triglycerides, total cholesterol, high-density lipoprotein cholesterol (HDL-C), low-density lipoprotein cholesterol (LDL-C), alanine transaminase (ALT), and γ-glutamyl transferase (γ-GT). Glucose levels will be measured by spectrophotometric techniques (AU5800, Beckman Coulter, Brea, California, USA). Insulin will be assessed by chemiluminescence immunoassay with paramagnetic particles (UniCel DxI 800, Beckman Coulter, Brea, California, USA). Triglycerides, total cholesterol, and HDL-C will be automatically evaluated by spectrophotometric techniques (AU5800, Beckman Coulter, Brea, California, USA). LDL-C will be considered as (Total cholesterol) − (HDL−C) − 0.45 ∗ (Triglycerides). ALT and γ-GT will be calculated by absorption spectrophotometric techniques (Beckman Coulter, Brea, California, USA). Insulin glucose ratio (insulin/glucose), LDL-C/HDL-C ratio (LDL-C/HDL-C), and triglycerides/HDL-C ratio (triglycerides/HDL-C) will also be determined.

##### Lifestyle Habits: Dietary Habits, Physical Activity, Smoking, and Alcohol Intake

Participants’ dietary habits will be evaluated using the validated 14-item Mediterranean diet screener (MEDAS), which evaluates food consumption frequency (12 items) and characteristic dietary habits of the Mediterranean diet (2 items) [39]. MEDAS items are scored with 0 or 1, the total score ranging from 0 to 14 points. The 22-item Food Behaviour Checklist (FBC) will also be used to assess participants’ food intake and habits [40]. FBC comprises seven subscales including consumption of fruit and vegetables (9 items), diet quality (4 items), fast food (3 items), dairy/calcium (2 items), sweetened beverages (2 items), meat (1 item) and food security (1 item). This instrument has been shown to be effective at evaluating dietary behaviour changes after nutrition education interventions promoting healthy diets [40].

Physical activity will be measured using daily step logs recorded by participants with a spring-levered pedometer (OcioDual, Alicante, Spain). Participants will be required to wear the pedometer all day and register the number of steps achieved per day in a seven-day step log. The average steps per day will then be calculated at baseline and follow-ups.

Regarding the remaining lifestyle habits, smoking and alcohol intake will be measured at baseline and follow-ups using seven-day self-reported tobacco and alcohol consumption logs. Recordings will include number of cigarettes/alcoholic units consumed per day, cigarette brand/type of alcoholic drink, time, situation, and perceived pleasure (from 0 to 10). The validated form of the Fagerström Test for Nicotine Dependence (FTND) [41] will also be used to assess participants’ nicotine dependence in all assessments.

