#### 2.6.2. Physical Exercise

Physical exercise has been shown to be effective in enhancing OSA outcomes and health-related consequences [1,78,79]. Due to the close association between OSA and obesity, a significant and sustainable increase of physical activity could lead to a reduced body weight and, in turn, improvement of the upper airway structure, function, and resting lung volume [12]. Furthermore, physical exercise could also assist the balance of energy intake and expenditure [80], and improve respiratory centre modulation through a reduction of the high leptin and ghrelin hormone levels, which are abnormalities linked to excessive energy intake found in OSA patients [81]. Yet, some research found that exercise benefits on OSA were independent to weight loss [79], suggesting that there are other related mechanisms potentially leading to OSA enhancement such as the increase of sleep efficiency and slow wave sleep [82], and a decrease of fluid accumulation implicated in the upper airway collapse [83], both due to the direct association between physical exercise and sleep.

Therefore, the INTERAPNEA study will include an eight-week physical exercise programme consisting of weekly 60 min sessions of supervised moderated aerobic exercise (i.e., 55–65% of the heart rate reserve) and individualised goal-setting to increase daily steps per week. Previous studies have emphasised that walking may be the exercise modality to achieve higher levels of weight loss and increased cardiorespiratory fitness in adults with obesity and CPAP-treated OSA [84]. Thus, in the weekly supervised training sessions, participants will be required to walk at a moderate intensity for 60 min wearing a heart rate monitor in order to train themselves to walk at that intensity during the week. With respect to goal-setting, they will be advised to increase their daily steps by 15% per week, based on their daily steps logs.

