### 2.8. Assessment of Compliance and Integrity of Intervention

Integrity of the intervention and treatment fidelity will be evaluated and ensured including the design and implementation of different strategies of process assessment, monitoring and enhancement in order to guarantee internal and external validity of the trial [95].

Firstly, regarding the study design and provider of intervention training, we developed a comprehensive hand-book for the qualified INTERAPNEA study intervention providers/professionals/training personnel of each module (nutrition, physical exercise, sleep hygiene, and tobacco and alcohol consumption). Each intervention manual identifies the theoretical model of the intervention and provides detailed descriptions of session objectives, treatment guidelines in accordance with each objective (i.e., contents, tasks and activities, recommendations, and timing), participant’s homework, and material needed for each session. We will also provide each participant with an adapted patient-handbook for each intervention component including descriptions of sessions, and work and logging sheets.

Secondly, we will ensure fidelity in the treatment delivery, receipt, and enactment through the use of these intervention protocols/manuals and monitoring of the implementation. Regarding the treatment delivery, the standardisation of the intervention will support the protocol adherence of providers and the treatment differentiation (i.e., the delivery of the target treatment and no other). Furthermore, we will include a check-list for provider’s self-report concerning the achievement of session objectives. With respect to the treatment receipt and enactment, fidelity will be assessed and confirmed through different strategies such as the structuring of the intervention around achievement-based objectives, collecting and reviewing of participants self-monitored data (daily steps log, sleep diaries, alcohol and tobacco consumption records), and information delivery in different formats (e.g., written in the handbooks, and verbal and visual in the sessions).

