Tobacco dependence and consumption	Self-reported tobacco consumption logs	Week 0, 9, 32
	The Fagerstrom Test for Nicotine Dependence	Week 0, 9, 32
Alcohol consumption	Self-reported alcohol consumption logs	Week 0, 9, 32
Physical fitness		
Cardiorespiratory fitness	2 km walk test	Week 0, 9, 32
Subjective physical fitness	International Fitness Scale	Week 0, 9, 32
Daily functioning and mood		
Functional outcomes related to sleepiness	Functional Outcomes of Sleep Questionnaire	Week 0, 9, 32
Subthreshold anxiety symptoms	State-Trait Anxiety Inventory	Week 0, 9, 32
Subthreshold depression symptoms	Beck Depression Inventory-Fast Screen	Week 0, 9, 32
	Inventario de Depresión Estado-Rasgo	Week 0, 9, 32

**Table 3 nutrients-11-02227-t003:** Description and timing of the INTERAPNEA intervention modules and components.

Module	Objectives/Description	Number of Sessions	Frequency of Sessions	General Behavioural Change Techniques
Nutritional behaviour change	Nutrition education and dietary patterns change	8	Once a week	Motivation and preparation for action Goal-setting and action-planning Self-monitoring and functional behavioural analysis Review of behavioural goals, action plans, and adherence Problem solving and social skills Self-efficacy, maintenance, and relapse prevention
Physical exercise	Supervised moderate aerobic exercise and increase daily steps by 15% each week	8	Once a week	
Sleep hygiene	Change of inappropriate sleep habits: Insufficient sleep, consumption of coffee, alcohol and tobacco, and inappropriate sleep schedule and environment	4	Once every two weeks	
Tobacco cessation	Nicotine and cigarette fading: Reduction of nicotine and number of cigarettes by 30% each week	8	Once a week	
Alcohol avoidance	Alcohol consumption fading: Reduction of alcohol consumption by 30% each week	4	Once every two weeks	

**Table 4 nutrients-11-02227-t004:** Description of nutrition education per session.

Session	Nutrition Education Topics
Session 1	Adverse consequences of obesity, importance of healthy nutrition and body composition on health, and positive effects of changes in nutrition.

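### The daily-step outcome comes from a self-kept log that is also the coaching and adherence record in the intervention arm, so target-driven over-recording can differ between arms

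*Protocol article*

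**What the plan says.** The step log has three uses in the protocol article.

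- **Outcome, both arms.** In Section 2.5.2 (Lifestyle Habits), "Physical activity will be measured using daily step logs recorded by participants with a spring-levered pedometer". Participants are to "register the number of steps achieved per day in a seven-day step log", and "The average steps per day will then be calculated at baseline and follow-ups". Table 2 lists "Spring-levered pedometer and daily step logs" at weeks 0, 9 and 32. Section 2.5 describes the baseline record as a "seven-day self-reported daily step log and sleep diary".
- **Goal-setting tool, intervention arm.** In Section 2.6.2, "they will be advised to increase their daily steps by 15% per week, based on their daily steps logs". Table 3 gives the module content as "Supervised moderate aerobic exercise and increase daily steps by 15% each week", over eight weekly sessions.
- **Enactment record, intervention arm.** Section 2.8 lists, among the ways treatment receipt and enactment are confirmed, "collecting and reviewing of participants self-monitored data (daily steps log, sleep diaries, alcohol and tobacco consumption records".

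Section 2.7 gives the control arm CPAP, general advice and leaflets, and describes no step goal or log review. Under Section 2.4.4 participants know their allocation, while staff who collect and analyse follow-up data are blinded. Section 2.5 places physical activity among the other variables of interest, below the primary outcome and the main secondary outcomes.

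**The concern.** An outcome should be measured the same way in both arms and independently of the treatment. Here the participant reads the count and writes it down, and he knows his arm. By week 9 an intervention participant has spent eight weeks working to a rising step target based on this log, which is collected and reviewed. A control participant meets the log only at assessments. Pressure to write a number close to the target therefore exists in one arm and not the other, and any resulting over-recording would appear as a treatment effect on activity.

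At stake is the reading of the step comparison and of anything built on it. Section 3 says the secondary outcomes may show which variables mediate or predict change in OSA. A step change that partly reflects coached recording would mislead there as well.

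**Working it through.** **1. Who records, and who is protected by blinding.** Section 2.4.4 blinds the staff who collect and analyse data. The step count is generated by the participant, who is not blinded. Staff blinding therefore does not reach this value.

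**2. Whether baseline adjustment helps.** Section 2.9 adjusts for the baseline value of the outcome. Section 2.4.4 randomises after baseline. A difference in recording caused by coaching arises after randomisation, so the baseline value carries no information about it and adjustment leaves it in place.

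**3. Whether another measure in the plan covers it.** For physical exercise habits Table 2 names only the pedometer and log. Section 2.5 mentions Day 2 questionnaires that touch on physical exercise, but no such instrument is named. The 2 km walk test measures fitness, not habitual activity.

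**4. How large the target is.** If 15% is compounded weekly, the goal relative to baseline is 1.15^7 = 2.66 after seven increases and 1.15^8 = 3.06 after eight. If 15% of baseline is added each week it is 1 + 7 × 0.15 = 2.05 and 1 + 8 × 0.15 = 2.20. This is intended real activity, not a bias estimate. It shows only that the participant knows how large a number is hoped for.

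**5. Size of a possible false difference.** The article gives no mean, SD or power figure for steps, so there is no plan figure to reproduce. The following are assumptions: baseline 6,000 to 8,000 steps/day, SD 2,500 to 3,500, no true change in either arm, and over-recording by a fraction b in the intervention arm only. The 35 per arm is the number before drop-out inflation in Section 2.4.1.

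False difference = b × baseline. Chance of a significant result favouring the intervention, two-sided 5% test = Φ(difference/SD × √(35/2) − 1.96), against 2.5% in that direction with no bias.

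| Baseline | b | False difference (steps/day) | In SD units (SD 3,500 to 2,500) | Chance of false significance (SD 3,500 to 2,500) |
|---|---|---|---|---|
| 6,000 | 5% | 300 | 0.09 to 0.12 | 5.5% to 7.2% |
| 6,000 | 10% | 600 | 0.17 to 0.24 | 10.7% to 17.0% |
| 6,000 | 20% | 1,200 | 0.34 to 0.48 | 30.0% to 51.9% |
| 8,000 | 5% | 400 | 0.11 to 0.16 | 6.9% to 9.8% |
| 8,000 | 10% | 800 | 0.23 to 0.32 | 15.8% to 26.7% |
| 8,000 | 20% | 1,600 | 0.46 to 0.64 | 48.1% to 76.3% |

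Example: 0.10 × 6,000 = 600; 600/3,000 = 0.20; 0.20 × √17.5 = 0.837; Φ(0.837 − 1.96) = 0.131.

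**The case against.** The strongest reply is that nothing in the article is false or contradictory. The baseline log is openly called self-reported, the outcome ranks low, and both arms keep their own logs at the same three assessments. The general effect of wearing a pedometer and watching the count is therefore shared. A reader might infer that recording error arises in one arm only; the documents do not support that. Only the part tied to coaching and targets can differ.

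A reader might also infer that the coaching device and the outcome device are the same. That is likely, since only one pedometer is described, but Section 2.6.2 does not say so. What the text does establish is that the step log serves both purposes.

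Three further replies carry weight. At week 32 no weekly target or session review is described, so the pressure to over-record should be weaker than at week 9. Fitness, weight and DXA are measured at the same time points and would give no support to a rise that existed only on paper, although they do not measure habitual steps. Device handling may be set out in the study manuals; but the article itself fixes who records the count and how the log is reused, and that is where the weakness lies.

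The tobacco and alcohol logs have a similar double use. That does not answer the point about steps.

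**Conclusion.** The point stands as a modest weakness in how one lower-ranked outcome is measured. The step outcome is not independent of the treatment, because the participant-kept log is also the intervention arm's goal-setting tool and enactment record. Differential over-recording is possible, most plausibly at week 9, and the stated safeguards do not remove it.

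The documents do not show that it will happen or how large it would be. The range of 300 to 1,600 steps/day rests wholly on assumed baselines and over-recording rates, and the chances of false significance rest also on the assumed SDs and 35 per arm.

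It would be wrong to infer that the trial's main conclusions are at risk: AHI, weight, DXA, blood markers and the walk test do not use the log. The consequence is confined to the step comparison and to any use of steps as evidence of changed activity or as a mediator.

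**What to change.** In the assessment weeks at 0, 9 and 32, in both arms:

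- cover the pedometer display;
- have participants tick only whether they wore the device each day;
- have the blinded assessors read the accumulated total at the visit and divide it by the number of days worn.

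Keep the open log for coaching during the eight weeks and report it as an adherence measure, not as the outcome.

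First confirm that the device accumulates counts over seven days, which the article does not state. If it does not, label the step outcome as self-recorded and not independent of treatment, and do not use it as evidence of changed activity or as a mediator of change in OSA.

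The cost is a cover, a tick sheet and one reading per visit on the existing device. Daily counts are lost in assessment weeks; the tick sheet is needed so that unworn days are not counted as low activity, and it remains self-reported. Covering the display does not prevent a real burst of walking in the assessment week.
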